### Intervention description {11a}

Intervention will start on the same day as children are confirmed eligible and caregivers have given their consent for participation. Children in the control group will not receive any nutritional treatment nor any other equivalent value non-food item. Children randomized to the simplified arm will all receive a nutritional treatment until being discharged. This nutritional treatment will consist of 1 sachet of RUTF per day for a maximum of 12 weeks or until reaching a WAZ ≥−3 for 2 consecutive visits. Children randomized to the standard arm will be categorized into 3 sub-groups: (1) those with a WHZ <−3, (2) those with a WHZ between −3 and <−2, and (3) those with WHZ ≥ −2. Children in the first sub-group will receive a weight-based RUTF dose that aims at providing 200 kcal/kg/day. The second sub-group will receive 1 sachet of RUTF per day. Both first and second sub-groups will be treated until WHZ ≥ −2 for 2 consecutive visits or for a maximum of 12 weeks. The third sub-group will receive no treatment. All children irrespective of their arm or sub-group will be followed up fortnightly until 12 weeks and then monthly until 24 weeks post-enrolment.

Exit criteria from treatment ire followed in the 2 intervention arms: standard and simplified treatment arms. Children in the control arm will not have exit criteria as they do not receive treatment and are only followed up.

Six exit categories exist from treatment: (1) recovery; (2) defaulting defined as missing 2 consecutive appointments at the treatment facility; (3) non-response, defined as not reaching the recovery criteria within 12 weeks; (4) died, defined as those cases of children that die during the trial, regardless of the reason of death; (5) transfer to inpatient care, defined as those cases that develop medical complications, as per the national protocol, and require inpatient treatment during the trial; (6) developing a MUAC <125 mm or edema.

Recovery is defined differently for children in the simplified and standard arm. In the simplified arm, recovery is defined as reaching a WAZ ≥−3 for 2 consecutive visits. In the standard arm, recovery is defined as reaching a WHZ ≥−2 for 2 consecutive visits. See Table 1 for the differences between arms.

**Table 1 Tab1:** Differences in intervention and end of intervention criteria between study arms

PROCEDURES	Control arm	Simplified treatment arm	Standard treatment arm

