Treatment provided	None	1 sachet of RUTF/day	Depending on the WHZ score: • WHZ <−3: 200 kcal of RUTF/kg/day • WHZ between −3 and −2: 1 sachet of RUTF/day • WHZ ≥−2: no treatment
Recovery criteria from treatment	None	WAZ >−3 on 2 consecutive visits	WHZ ≥−2 on 2 consecutive visits

All other exit categories except for MUAC <125 mm or edema or died continue in the study unless the caregiver is not willing to do so. All children requiring inpatient-level care will be referred to the health center’s head nurse or doctor for them to prepare a formal referral of the patient to inpatient care.

Children will be classified in 5 different categories at the exit from the study: (1) finished 6-month follow-up, (2) developed MUAC <125 mm or edema during follow-up and was referred to routine treatment, (3) abandoned study, (4) lost-to-follow-up, (5) died. Abandoned will be defined as those who do not come back to study visits but who have been contacted to confirm the child is still alive. Lost-to-follow-up will be defined as those who do not come back to study visits and who have not been reached to confirm whether the child is still alive.

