### Outcomes {12}

Both primary and secondary outcomes will be reported for all 3 arms at both 2 (primary endpoint) and 6 months (secondary endpoint) post-enrolment. The primary outcome is the mean WAZ of children. WAZ has been shown to be strongly associated with mortality and thus acts as a proxy of the ultimate goal of reducing child mortality. Increase in WAZ can be both related to the increase in HAZ or WHZ, which is an added value as it enables appreciating and aggregating both outcomes that are positive. As a continuous measure, WAZ is well adapted to capture the response to treatment among the study population as it will more easily capture smaller benefits of treatment compared to categorical outcomes.

Secondary outcomes include (a) proportion of children with WAZ <−3, (b) mean MUAC of children, (c) mean WHZ and HAZ, (d) proportion of children with WHZ <−3 or HAZ <−3, (e) mean skinfold thickness measures and mean skinfold thickness per age percentile, (f) mean fat-free mass and fat mass, fat-free mass index and fat mass index, (g) mean hemoglobin measure, and (h) change in all these outcomes from enrolment to endpoint. In addition, the proportion of children exiting the study at any time point due to a MUAC <125 mm or edema or diseased or hospitalized will be reported across arms. Finally, treatment outcomes will be reported for the 2 treatment groups including the percent recovered, defaulted, non-response, transferred to inpatient care, and died. The study exit status will be reported for all 3 arms including completion of the 6-month follow-up, developed a MUAC <125mm or edema during the study, abandoned study, lost-to-follow-up, and died.

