### Methods in analysis to handle protocol non-adherence and any statistical methods to handle missing data {20c}

All analyses will be carried out in an all available case basis, i.e., all study participants will be included in the analysis. In case of missing outcome data at the primary and secondary endpoints of 2 and 6 months respectively, imputation will be performed using key variables such as age, sex, time since enrolment, randomization arm, treatment status, other anthropometry, and any other (previous or later) outcome measure data points. The primary analysis will apply a “de facto” principle [51] answering to the question of whether the treatment works in a real-life setting, and will thus analyze the data irrespective of degree of adherence to their treatment group. In addition, a “de jure” analysis will be performed to estimate the efficacy of the treatment in a best-case scenario, adjusting for the actual dose obtained, simulating a per-protocol analysis, as per the recommendations for non-inferiority analysis [52, 53]

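### The supplementary de jure analysis adjusts for RUTF dose received, which is itself the contrast between the simplified and standard arms, so it is no per-protocol check on non-inferiority

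*Protocol article*

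**What the plan says.** All references are to the protocol article.

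- **Analysis (section 20c).** The primary analysis is de facto: it will "analyze the data irrespective of degree of adherence to their treatment group". A second, de jure analysis is meant to estimate best-case efficacy by "adjusting for the actual dose obtained, simulating a per-protocol analysis, as per the recommendations for non-inferiority analysis".
- **Outcome (section 12).** "The primary outcome is the mean WAZ of children", with the primary endpoint at 2 months.
- **Simplified arm (section 11a).** Children receive "1 sachet of RUTF per day for a maximum of 12 weeks or until reaching a WAZ ≥−3 for 2 consecutive visits".
- **Standard arm (section 11a and Table 1).** There are three sub-groups by WHZ. For WHZ below −3: "Children in the first sub-group will receive a weight-based RUTF dose that aims at providing 200 kcal/kg/day". For WHZ from −3 to below −2: "The second sub-group will receive 1 sachet of RUTF per day". For WHZ of −2 or more: "The third sub-group will receive no treatment". The two treated sub-groups stop once WHZ is at least −2 at two visits running, or at 12 weeks.
- **Everything else.** The visit schedule (section 11a) and the clinical examination (section 18a) are the same in all arms.

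**The concern.** Dose received is not a measure of adherence here. It plays two other roles, and both spoil it as a covariate.

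1. **It is the treatment contrast.** The two arms compared for non-inferiority differ in the amount and duration of RUTF and in nothing else that the protocol describes. If the arm acts on WAZ through RUTF, holding RUTF constant leaves a residual direct effect near zero.
2. **It is a consequence of response.** In the simplified arm RUTF stops when WAZ, the primary outcome variable, passes a threshold. In the standard arm it stops on WHZ. Fast responders therefore collect fewer sachets, and the adjustment brings in confounding by growth.

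Nor does dose identify protocol-compliant children. A standard-arm child with WHZ of −2 or more who takes nothing is fully adherent, and so is a simplified-arm child who stops on recovery. Both would enter the model as low exposure.

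At stake is the corroboration of the non-inferiority result. The protocol presents this analysis as the one recommended for non-inferiority, so agreement with the de facto result would be read as support that it cannot give.

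**Working it through.** **Plan's own figures.** With SD 1.1, margin 0.2, one-sided 2.5% and 80% power, n = 2 × 1.1² × (1.96 + 0.84)² / 0.2² ≈ 475 per arm. Allowing for 20% missing, 475 / 0.8 = 594. The total is 594 + 594 + 209 = 1397. All three reproduce. The point below changes none of them.

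**Algebra.** Suppose Y = a + s·D + e, where D is sachets received by 2 months and s is WAZ gain per sachet. The total arm effect is s × (mean D simplified − mean D standard). The arm coefficient with D in the model is 0, whatever that total is.

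**Dose depends on response.** Enrolment requires WAZ below −3, and visits are fortnightly, so two qualifying visits can first occur at weeks 2 and 4. By week 8 a fully adherent simplified-arm child may have taken 28 sachets (fast responder) or 56 (never qualifying). Fewer sachets then go with better growth.

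**Which arm gets more RUTF.** Assume 500 kcal per sachet and 7.5 kg body weight. Then 200 × 7.5 / 500 = 3 sachets/day for WHZ below −3. The standard arm's mean excess at enrolment is (3 − 1) × p₁ + (1 − 1) × p₂ + (0 − 1) × p₃ = 2p₁ − p₃, where p₁, p₂ and p₃ are the shares with WHZ below −3, from −3 to below −2, and −2 or more.

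| Assumed mix p₁/p₂/p₃ (%) | 2p₁ − p₃ (sachets/day) |
|---|---|
| 20/50/30 | +0.10 |
| 35/45/20 | +0.50 |
| 50/40/10 | +0.90 |
| 70/25/5 | +1.35 |
| 10/40/50 | −0.30 |

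The sign turns once p₃ exceeds 2p₁.

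**Simulation.** This used 475 per arm, the doses and stopping rules of section 11a, 8 weeks and 400 replicates, with least squares on arm and baseline WAZ, with and without received dose. The following inputs were assumed because the protocol gives none of them: WHZ mix, s of 0.005 or 0.008 WAZ per sachet, weight 6–10 kg, mean adherence 85%, 500 kcal per sachet, and a latent growth tendency with SD 0 to 0.6. The difference is simplified minus standard, and P(NI) is the share of replicates declaring non-inferiority.

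| Mix (%) | s | Growth SD | Unadjusted | Dose-adjusted | P(NI) unadjusted | P(NI) dose-adjusted |
|---|---|---|---|---|---|---|
| 20/50/30 | 0.005 | 0 | −0.051 | −0.001 | 1.00 | 1.00 |
| 35/45/20 | 0.008 | 0 | −0.252 | 0.001 | 0.00 | 1.00 |
| 35/45/20 | 0.008 | 0.6 | −0.247 | −0.040 | 0.002 | 0.952 |
| 50/40/10 | 0.005 | 0.6 | −0.255 | −0.053 | 0.00 | 0.898 |
| 70/25/5 | 0.008 | 0.6 | −0.593 | −0.115 | 0.00 | 0.38 |

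With no latent growth, the adjusted coefficient was about 0.00 for every true difference from −0.05 to −0.60. With latent growth it moved to between −0.01 and −0.12, which matches neither zero nor the true effect. A further check found the same collapse in both directions: −0.41, −0.19 and +0.07 each went to 0.00.

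**Caution on P(NI).** The residual SD after dose adjustment in these runs is at most about √(0.6² + 0.2²) = 0.63, below the plan's 1.1. On the plan's SD, SE = 1.1 × √(2/475) = 0.071 and the interval half-width is 0.14. A coefficient centred at 0 would then pass with probability Φ(0.2/0.071 − 1.96) ≈ 0.80, less whatever precision is lost to the correlation of dose with arm. A coefficient centred at −0.25 would pass with probability about 1 − Φ(0.19/0.071) ≈ 0.004. The gap remains large.

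**Alternative reading.** When the share of prescribed dose taken was used in place of dose, the contrast survived (for example −0.252 unadjusted and −0.253 adjusted).

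**The case against.** **The wording may mean adherence.** Section 20c concerns non-adherence, and section 19 checks RUTF received against what the arm and the child's measurements call for. The phrase could therefore mean dose relative to the dose assigned, which would keep the contrast. This stands as a possible intention, but the text does not say it. The ratio is also undefined for standard-arm children assigned no RUTF. The wording needs correcting on either reading.

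**Three stronger readings are tempting, and the document does not support them.**

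- *That the trial's non-inferiority claim fails.* The de facto analysis is primary and untouched, and nothing in the protocol makes the conclusion depend on the de jure result.
- *That the adjustment always favours non-inferiority.* The direction follows the WHZ mix, which is not given. The mixes tabulated in the simulation all lie on the side where the standard arm gives more RUTF; at 10/40/50 the sign reverses. A calculation confined to children with WHZ below −3 (3 versus 1 sachets/day, −0.22 becoming 0.00) describes one stratum, not the pooled comparison.
- *That the comparison with no treatment is distorted by a known amount.* Dose is zero for every control child, so arm and dose could be separated only by extrapolation. But the protocol ties this analysis to non-inferiority, and section 8 gives the control arm a part in the superiority test only. No size is claimed for that comparison.

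**Conclusion.** The point holds for the supplementary de jure analysis as worded. Adjusting for received dose removes the contrast between the simplified and standard arms and adds confounding by response, so the result cannot corroborate non-inferiority. The collapse towards zero follows from the design, provided that the arms act on WAZ through RUTF; the protocol describes no other difference between them.

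The sizes are illustrative. True differences of about −0.25 to −0.60 WAZ became 0.00 to −0.12. At about −0.25, beyond the 0.2 margin, non-inferiority was declared in 90–100% of simulated trials with dose adjustment and in 0–0.2% without it. All of this rests on the assumed WHZ mix, dose-response, weights, adherence and sachet energy. The same adjustment would hide inferiority where the standard arm gives more RUTF on average, and an advantage of the simplified arm where non-wasted children predominate. The primary analysis and the sample size are unaffected.

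**What to change.** In section 20c, replace adjustment for the dose obtained with an analysis based on adherence to the assigned regimen:

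- Define adherence as RUTF taken divided by RUTF due under the child's own arm and sub-group, up to that child's stopping rule.
- Count a child assigned no RUTF as adherent if none was taken.
- Keep received dose out of the outcome model.
- Account for baseline and prior-visit predictors of adherence, for example by inverse-probability weighting, because adherence is itself a post-randomisation variable.

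A rule that non-inferiority must hold in both analyses would be a separate decision, which this error does not call for.

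The cost is a change of wording and a little more analysis work. Intake questions and returned sachets (section 11c) and the concordance check (section 19) already supply the data. The wording should be settled before the analysis, which the trial status section places after the end of follow-up.

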### Plans to give access to the full protocol, participant-level data, and statistical code {31c}

The last version of the full study protocol and standard operating procedures will be published with the article on the main outcomes of the trial. Deidentified participant-level data will be made publicly available on Zenodo once primary analyses are ready. The statistical code for all analyses reported in peer-reviewed articles will be included as supplementary files of the article.

## Oversight and monitoring

### Composition of the coordinating center and trial steering committee {5d}

This trial has been designed and set up in collaboration between the International Rescue Committee, University of Sciences, Technics and Technologies of Bamako (USTTB), and the Ministry of Health and Social Development (MoHSD) of Mali. The co-investigator group is composed of 2 researchers from the IRC, 1 researcher from USTTB, and 1 nutritionist from the MoHSD of Mali. This group will be meeting at least monthly during the trial to review trial progress and discuss any implementation issues and needs for revisions to protocol or implementation procedures.

The day-to-day study activities will be managed by a full-time study manager based in Nara, supported by a deputy manager. Four field teams will be performing the actual study intervention and data collection, and a total of 8 pre-screeners will be deployed in the community to screen children based on the eligibility criteria. Each field team will be composed of 5 members including 2 polyvalent agents in charge of the consent process, anthropometric measurements, questionnaires, and body composition measurements, 2 study nurses who will perform clinical checks, hemoglobin measurements, and prescribe and administer any medication and 1 supervisor that will supervise the team, administer the nutritional treatment according to the study arm and compensate participants at each visit. The full field team will be meeting monthly to discuss any implementation issues and be re-trained on processes as needed.

Data will be managed by 2 data managers who will be reviewing data quality and progress of implementation on a weekly basis. A list of data points for double-checking will be shared weekly with the field team in order to flag data points that seem unusual and where cross-checking of electronic data is needed against any paper forms. These flags can for example be unusually high increases in weight between 2 consecutive measurements, or any decrease in height over time. A data review meeting will be held fortnightly involving the data managers, the study manager, and 2 investigators to alert the team on any specific issues and decide on actions (training or other). The data reviews will include checking the baseline balance between randomization groups, quality of outcome data collected and completeness of data collected, and quality of intervention. Only baseline data will be stratified per arm to monitor randomization success while outcome data will be kept separate from the randomization code to avoid pre-mature conclusions of the trial.

The trial is guided by a scientific committee of experts in pediatrics, humanitarian nutrition, epidemiology, and statistics from the London School of Hygiene and Tropical Medicine, University of Copenhagen, University of Tampere, Brixton Health, and National Institute of Public Health Denmark. This group will be receiving updates on the trial progress and will be involved in any decisions to revise protocol or implementation processes.

### Composition of the data monitoring committee, its role and reporting structure {21a}

A DSMB, comprising of independent members with experience in nutrition epidemiology and humanitarian nutrition, will review the outcomes and adverse events at mid-point of the trial. The committee is composed of a President and a Statistician. The president will be responsible for convening meetings at suitable intervals and communicating with the investigator group on the committee’s work and decisions. The statistician will be responsible for performing the interim analyses. Both members will decide together on the timing and data included in the interim analysis and will be involved in the discussion on the findings and recommendations to be made to the investigator group.

### Adverse event reporting and harms {22}

All serious adverse events will be immediately reported to the study supervisor and the child referred to inpatient treatment if needed. Serious adverse events include death, development of any grade of edema, development of a MUAC<125mm, and development of medical complications requiring inpatient care. In case of death, an investigation to the cause of death will be made within 48 h of the information and a report will be written and forwarded to the DSMB and IRBs within 72 h.

### Frequency and plans for auditing trial conduct {23}

Three study investigators, 1 from IRC, 1 from USTTB, and 1 from MoHSD Mali will be performing field supervision to monitor the respect of the study processes. A week-long field supervision is planned for every 3 months. In addition, the study manager and their assistant will perform regular (weekly) field supervision to monitor the respect of the ethical and other implementation processes.

### Plans for communicating important protocol amendments to relevant parties (e.g. trial participants, ethical committees) {25}

Any changes to the study protocol, unless the recommendation comes from the DSMB, will require ethical approval prior to implementation, both from the IRC IRB and the ethics committee of the USTTB. Changes will be communicated to the study Scientific Advisors through email and the study participants verbally by field team supervisors and to the community through community focal points.

### Dissemination plans {31a}

The investigators plan to communicate the study results at the community, district, national, regional, and global level through presentations and discussions with relevant groups the investigator group are engaged with. At the community level, this will include holding debriefings of the project with the community focal points (*n*=200) that will be in charge of transmitting the messages to the study participants and communities. At the district level, this includes the Head Physician of the District, the District Health Lead team, and the Heads of the participating health centers and their nutrition focal points. At the national level, these include the Malian Nutrition Technical Group which involves all national nutrition actors including the MoHSD Sub-Division of Nutrition, UNICEF, WFP, and implementing non-governmental organizations (NGOs). Results will also be discussed with the Malian MoHSD Sub-Division of Nutrition to draw locally adapted recommendations. At the regional level dissemination activities will include a presentation and a discussion with the West- and Central-Africa Regional Nutrition Working Group sub-group on wasting which is headed by UNICEF. At the global level dissemination activities will include presentations and discussions with the Global Nutrition Technical Alliance, the Wasting Stunting Technical Interest Group which includes prominent nutrition researchers working in this sphere, and the Simplified Approaches Working Group.

## Discussion

This individually randomized controlled 3-arm trial evaluates the response to treatment of children with WAZ <−3 but MUAC ≥125 mm when treated with a simplified protocol versus standard protocol versus no treatment. If the results show that treatment is superior to no-treatment then this speaks for adding WAZ as an additional and independent admission criteria to MUAC <125 mm to treatment. If this study shows that the simplified treatment is non-inferior to standard treatment, then this contributes to the growing evidence base that the simplified protocol is as effective as the standard protocol in correcting childhood malnutrition.

## Trial status

Recruitment of trial participants began on the 29th of August 2022 and was completed in October 2023. Follow-up of the last patients should then be finished by the end of April 2024, at which point data will start being analyzed. This protocol is version number 3.2 dating 15 November 2022.

